## Abstract

**Background:**

Oral health behaviours such as establishing twice-daily toothbrushing and sugar control intake need parental self-efficacy (PSE) to prevent the development of childhood dental caries. A previous study has shown that behaviour change techniques (BCTs) delivered via a storybook can improve parental self-efficacy to undertake twice-daily toothbrushing. Objective: to determine whether an intervention (BBaRTS, Bedtime Brush and Read Together to Sleep), designed to increase PSE; delivered through storybooks with embedded BCTs, parenting skills and oral health messages, can improve child oral health compared to (1) an exactly similar intervention containing no behaviour change techniques, and (2) the BBaRTS intervention supplemented with home supply of fluoride toothpaste and supervised toothbrushing on schooldays.

**Methods/Design:**

A 2-year, three-arm, multicentre, cluster randomised controlled trial. Participants: children (estimated 2000–2600) aged 5–7 years and their families from 60 UK primary schools. Intervention: Test group 1: a series of eight children’s storybooks developed by a psychologist, public health dentist, science educator, children’s author and illustrators, with guidance from the Department for Education (England). The books feature animal characters and contain embedded dental health messages, parenting skills and BCTs to promote good oral health routines focused on controlling sugar intake and toothbrushing, as well as reading at bedtime. Books are given out over 2 years. Test group 2: as Test group 1 plus home supplies of fluoride toothpaste (1000 ppmF), and daily supervised toothbrushing in school on schooldays. Active Control group: series of eight books with exactly the same stories, characters and illustrations, but without BCTs, dental health messages or parenting skills. Annual child dental examinations and parental questionnaires will be undertaken. A sub-set of participants will be invited to join an embedded study of the child’s diet and salivary microbiota composition. Primary outcome measure: dental caries experience in permanent teeth at age 7–8 years.

**Discussion:**

A multi-disciplinary team was established to develop the BBaRTS Children’s Healthy Teeth Programme. The books were developed in partnership with the Department for Education (England), informed by a series of focus groups with children, teachers and parents.

**Trial registration:**

ISRCTN21461006 (date of registration 23 September 2015).

## Background

Past caries experience in the primary teeth is the strongest predictor of caries occurrence in the permanent dentition [1]. The first permanent molar teeth, which are the most caries-prone teeth, begin to erupt after the fifth birthday and are mainly fully erupted during the sixth year [2]. They are most vulnerable to caries development within the first year of eruption [3]. Decay experience in these teeth account for the majority of decay in children and result in lifelong impacts and costs [4]. Therefore, preventing decay experience in these teeth would result in significant savings to dental service costs and enhanced children’s oral quality of life.

Dental caries is an entirely preventable disease and there is comprehensive guidance on prevention for dental teams working in the National Health Service (NHS) in England [5] and in Scotland [6] to advise families on brushing twice daily with fluoridated toothpaste, controlling dietary sugars’ intake especially at bedtime, and for those children at high risk, (e.g. with caries experience in primary teeth) to provide evidence-based clinical procedures including fissure sealants and fluoride varnish. National guidance has been developed for the frequency of dental attendance and recall linked to disease risk category [7] and a systematic use of risk categorisation is being piloted in the new dental contract in England [8, 9]. Dental caries preventive guidance is aligned with general public health recommendations for adopting a healthy diet low in free sugars to prevent obesity [10]. These general health messages and supporting skills are delivered in a wide range of both local authority and NHS programmes and settings.

However, there is strong evidence of stark oral health inequalities rooted in the social determinants of oral and general health. For caries development, the difference between a healthy state and disease initiation and progression relates to the balance between the amount and frequency of consumption of free sugars, and other potentially fermentable carbohydrates, that are metabolised by the bacteria in dental plaque producing acids as metabolic bi-products, leading to demineralisation of teeth and the presence of a favourable oral environment for remineralisation including adequate levels of fluoride [11]. In the absence of water fluoridation, the population approach to optimise fluoride exposure is through the establishment and maintenance of twice-daily toothbrushing with fluoridated toothpaste [12]. Both control of free sugars’ intake, especially at bedtime, and twice-daily brushing rely on the development and maintenance of healthy routines at home from a young age. The likelihood of these occurring is socially and culturally patterned, and depends on parental self-efficacy to establish the behaviours [13] with a supportive personal and community environment that sees these as normal and provides the skills and materials to make these choices natural and accessible.

However, in socially disadvantaged communities, there are significant barriers to establishing healthy behaviours and providing supportive community environments, leading to oral health inequalities, and unequal uptake of dental care. Bringing preventive methods into school settings can be an effective route to supplement and support behaviours and care, which may not have developed into consistent daily routines at home. Providing a home-to-school support programme can promote the development of oral health [14, 15]. The consequences of dental caries in schoolchildren manifests in pain and sepsis; lost days from school for children; and from work for parents and carers [16]. The effects of poor dental health in primary school children impact daily living and functioning; cause lost time and concentration on learning; increased costs to primary medical and dental care; and for those worst affected increased hospital costs due to dental extractions under general anaesthesia (GA) resulting in short-term and lifelong impacts [16–19]. Therefore, approaches which only treat the symptoms of the disease are costly both to individual children and families, and also to the NHS.

Different methods of primary and secondary prevention are advocated [11]. A medical model approach seeks to identify those at high risk of the disease and treat them, as with the approach to high serum cholesterol [20]. A population approach seeks to change the ambient environment both in terms of reducing the availability and acceptability of foods and drinks containing free sugars (e.g. by increasing their cost) and by enhancing community availability of fluoride (e.g. by increasing use of fluoride toothpaste through community programmes). The former, medical model approach would require a commissioner of NHS dental services to consider how dental contracts might be structured to enhance access to services and provide care. The latter, population approach, might engage local authorities (in England) in deciding on the type of community intervention to support to promote the oral health of schoolchildren. It is, therefore, critical to determine both the cost and effectiveness of different approaches, particularly in an environment of limited resource where there is a need to optimise investment. There is limited information available of the highest quality to accurately inform this choice for those commissioning services in these disadvantaged communities [21].

The design of this study has been based on the results of a major international study which indicated that the most significant variable predicting whether children were most likely to be caries-free was parents’ perception of their ability to successfully deliver child toothbrushing and control of sugar eating and drinking (‘sugar snacking’) behaviours, i.e. parental self-efficacy [22]. A previous proof-of-concept study by the authors has shown that a storybook approach can be used to improve parental self-efficacy to undertake twice-daily toothbrushing [23]. The age of the children at commencement of this trial has been chosen to be 5–7 years. Children begin school in the UK at age 5 years, and between 5 and 7 years their first permanent molar teeth erupt [24]. Therefore, an intervention study conducted to include this post-eruption period provides a pivotal time to evaluate primary prevention of dental caries in permanent teeth.

### Aim

The primary aim of this research is to determine whether children’s dental health can be improved by increasing parental self-efficacy using a storybook approach for two child behaviours: toothbrushing and reducing consumption of free sugars. Specifically, with the following objective:

### Objective

To determine whether an intervention (Test group 1) designed to increase parental self-efficacy using a storybook approach with embedded behaviour change techniques (BCTs) for two child behaviours (toothbrushing with fluoride toothpaste and reducing consumption of free sugars to within recommended levels [25], especially at bedtime) can improve child oral health compared to (1) an exactly similar intervention without embedded BCTs (Active Control) and, (2) the intervention (Test group 1) supplemented with home supply of fluoride toothpaste and supervised toothbrushing on schooldays (Test group 2).

### Research questions

Can child dental health be improved by increasing parental self-efficacy using a behaviour change intervention delivered by storybooks for two child behaviours: toothbrushing and ‘sugar snacking’? (Control versus Test group 1)Can child dental health be improved by an enhanced intervention designed to improve parental self-efficacy using a behaviour change intervention delivered by storybooks for two child behaviours: toothbrushing and control of ‘sugar snacking’ *plus* home supply of fluoride toothpaste and supervised toothbrushing with fluoride toothpaste at school? (Control versus Test group 2)Does the addition of home supply of fluoride toothpaste and supervised toothbrushing with fluoride toothpaste at school increase the effectiveness of an intervention designed to improve parental self-efficacy using a storybook approach for two child behaviours: toothbrushing and ‘sugar snacking’? (Test group 1 versus Test group 2)

For a sub-study of the main study:Does an intervention designed to improve parental self-efficacy using a behaviour change intervention delivered by storybooks for two child behaviours: (toothbrushing and ‘sugar snacking’) result in changes to parental-reported child consumption of free sugars? (Control versus Test group 1)Does the addition of home supply of fluoride toothpaste and supervised toothbrushing with fluoride toothpaste at school increase the effectiveness of an intervention designed to improve parental self-efficacy using a storybook approach with embedded BCTs for two child behaviours (toothbrushing and ‘sugar snacking’) result in changes to parental-reported child consumption of free sugars? (Test group 1 versus Test group 2)Does an intervention designed to improve parental self-efficacy using a behaviour change intervention delivered by storybooks for two child behaviours (toothbrushing and ‘sugar snacking’) result in changes to the cariogenic profile of children’s microbiota? (Control versus Test group 1)Does the addition of home supply of fluoride toothpaste and supervised toothbrushing with fluoride toothpaste at school increase the effectiveness of an intervention designed to improve parental self-efficacy using a behaviour change intervention delivered by storybooks for two child behaviours (toothbrushing and ‘sugar snacking’) result in to the cariogenic profile of children’s microbiota? (Test group 1 versus Test group 2)

## Methods/Design

This is a three-arm, multicentre cluster randomised controlled trial (RCT), with blinded outcome assessment.

### Ethics, consent and permissions

Research ethics and governance approval has been obtained for this study from the Queen Mary Research Ethics Committee (ID: QMREC2013/43). Informed consent will be obtained for each participant.

### Main study sample and recruitment

Participants will be identified from primary schools in England and Scotland, whose head teachers have agreed to participate in the study. At the beginning of the school term parents of all children entering class 1 (5–6 years) will be sent an information pack and informed consent document via schools. All participants will be given reasonable time to consider the study and discuss with their family. Members of school staff will be able to answer questions and contact details for the study team will be on the information sheet.

Parents who complete the informed consent document and return it to the school will be given the baseline questionnaire to complete and return to the child’s teacher.

### Inclusion and exclusion criteria for main study

Inclusion criteria: children, aged 5–6 years, who are attending state-maintained primary schools in Kent and Newham in England, and Tayside in Scotland in which the school head teacher has given permission for their school to be included in the trial will be included in the study, subject to their parents giving written consent.

Exclusion criteria: children of the same age, in the same schools for whom parents have not given written permission for their children to take part.

### Sub-study sample, recruitment and data collection

Parents of participants in the schools in Tayside, Scotland who are already participating in The BBaRTS trial will be sent an information pack and informed consent document for the sub-study via schools. The sub-study will seek parental consent for collection of data on food and drink intake over a 3-day period using the Intake24 multiple-pass 24-hour recall system (https://intake24.co.uk) [26] or as a paper-based 3-day food and drink diary (to be entered into Intake24 by the researchers). Children will be included in the sub-study, subject to written parental consent; and will be excluded from joining the sub-study in the absence of written parental consent. In addition to parental completion of a 3-day food and drink diary, children included in the sub-study will also have a sample of unstimulated saliva collected at baseline and study end (after 2 years). It is expected that the Scottish cohort of the trial will include around 400 children and it is anticipated that about 50 % of their parents (*n* = 200) will give consent to join the sub-study.

The saliva samples will be collected using the following method. Sterile collection bottles will be prepared with a label affixed with the child’s identification (ID) number. The research dental nurse will have three items for each subject: a pre-labelled collection bottle, a sterile pipette and a small sterile sample bottle. The nurse will visit the schools and bring together, in small groups, the children from whom a saliva sample will be requested. Each child will be given a collection bottle and, under nurse supervision, the top of the bottle will be removed. Each child will be asked to lean their head forward and dribble saliva from their mouth into their collection bottle. No stimulation will be provided in the way of paraffin wax and children will be asked to gently drool the saliva naturally collecting in their mouth rather than spitting. Tissues will be provided to the children to wipe off excess saliva from their mouths. Once a sample exceeding 1 ml has been collected in the bottle, the research dental nurse will screw the top back onto each bottle. Any child who cannot provide a sample will be given extra time but if no sample is forthcoming, the child will be excused the collection and reassured. The children will be escorted back to their classroom and, before leaving the school, the nurse will pipette 1 ml of saliva from the collection bottle to the child’s small sample bottle, which the nurse will label with the child’s ID number. These small sample bottles will be put into a rack which allows the sample bottles to stand upright and be stored individually. The lid of the rack will be closed forming a container which will be put into a freezer box, which will contain frozen blocks. The freezer box will be transported back to the clinic base where the containers with the samples will be placed in a domestic refrigerator and transported under dry ice to the laboratory within 2 days. All samples will be placed in a freezer in the microbiology laboratory at −80 °C

### Data collection for main study

#### Primary outcome

Dental caries experience in permanent teeth at age 7–8 years.

Dental examinations will be conducted in the child’s school. The examinations will be conducted by independent dental examiners, trained in standardised dental epidemiological survey techniques [27] and blinded to the group allocation of the school. Dental caries experience on any surface in either dentition will be recorded. All children will be examined using sterilised or single-use mouth mirrors, Community Periodontal Index of Treatment Needs (CPITN) probes, a standardised dental examination lamp (2000 lux) and cotton wool rolls as needed.

This assessment will be analogous to national dental screening in schools, which is a simple visual assessment of the child’s teeth. Children will be asked to assent to the examination. Any child who does not assent and refuses to have their teeth checked will remain in the study and will not be excluded; the dental examination data will be recorded as missing data for that assessment. Teachers and parents will be informed prior to each assessment that these assessments are a simple observational screening and are not a replacement for the children’s dental examinations from their family dentist.

#### Secondary outcomes

Dental caries experience in permanent teeth at age 6–7 years (midpoint).

Oral cleanliness will be measured by plaque assessment on the buccal surfaces of upper anterior teeth at dental examinations [28].

Parents/guardians of children will be asked to complete a questionnaire pack at baseline, 1 year and 2 years post enrollment. This will be sent home and collected via the school. Questionnaires will take approximately 20 minutes to complete, incentives for completion of questionnaires will not be offered. Measures at 1 and 2 years will be secondary outcomes.Oral Health Behaviours QuestionnaireThis is a validated measure examining parental attitudes, beliefs and behaviours towards dental care and includes parental self-efficacy [13]Faces IV Family Satisfaction ScaleThis is a validated family self-report measure of family satisfaction with how the family operates on a day-to-day basis [29]Early Childhood Oral Health Impact ScaleThis validated scale measures oral health-related quality of life [30]Reading IntensityThis scale is modified from earlier research undertaken by the team and measures parental- reported frequency of reading storybooks to their child [23]

#### Sub-study outcomes

Measurement of free sugars’ intake and other dietary variables.

Intake24 will be used to collect dietary information from a sub-sample of the study population. Intake 24 (https://intake24.co.uk) is a participant-completed computerised dietary recall system based on multiple-pass 24-hour recalls. In this study it will be used to collect dietary information over three consecutive days. From this, the energy intake (kcal/day) and the daily amount (g/day and percentage contribution to total energy intake) and daily frequency of intake of free sugars, the percentage contribution of specific food sources to free sugars’ intake will be derived. The intake of milk and intrinsic sugars (g/day and % energy), total sugars (g/day and % energy) intake of processed starchy foods (g/day and contribution to energy intake), intake of staple starch rich foods (staples) (g/day and % energy) will also be determined. The contribution to intakes made by defined food groups (e.g. biscuits and cakes, confectionery and drinks) will be determined.2.Profile of oral microbiota, specifically *Streptococcus mutans,* lactobacilli and other caries-related bacterial taxa.

DNA will be extracted from unstimulated saliva samples and V1–V2 of the 16S ribosomal RNA genes of bacteria in the samples will be sequenced by means of the Illumina MiSeq platform using a dual-indexing barcoding approach. Sequencing will be performed using a 2 × 300 flow cell for paired-end sequencing. Sequences will be analysed using the mothur pipeline [31], following the MiSeq SOP. Operational taxonomic units (OTUs) will be constructed at the 98.5 % similarity level. OTUs will be identified with reference to the Human Oral Microbiome Database reference dataset [32, 33]. Distance matrices, generated with the Jaccard Index and thetaYC metric, will compare sample β-diversities based on OTUs and visualised as dendrograms and three-dimensional Principal Co-ordinates Analysis (PCoA) plots (generated in R). Analysis of Molecular Variance (AMOVA) will be performed to determine if clustering patterns seen in the PCoA plots are statistically supported by differences in the distance matrix. Differentially abundant OTUs between patient groups of interest will be identified using the LDA Effect Size (LEfSe) algorithm [34]. Proportions of mutans-group streptococci, lactobacilli, *Bifidobacteriaceae* and *Propionibacterium acidifaciens* will be compared across intervention groups using appropriate statistical tests depending on the data distribution.

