### Randomisation

Following the collection of consent forms from parents and collection of baseline dental and questionnaire data, schools will be randomised to Test group 1 (test books only), Test group 2 (test books and fluoride toothpaste), or Control (control books). The study flow in each group is presented in Fig. 1.

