#### Sample size

Previous study and pilot study data on similar populations have shown that there is likely to be virtually no caries in first permanent molars at baseline, and most teeth will be unerupted [15]. As the study is cluster randomised, the intra-cluster correlation coefficient (ICC) must be considered when calculating sample size. Few estimates of school-level ICC are available for dental data, so a value of 0.01 was used, based on unpublished data collected by the authors. To allow for participant dropout and non-consent, it is assumed that an average of 30 pupils per school will participate and have primary outcome data available at study end. If the caries incidence in the control group is 35 %, the observed value in a previous study in a deprived population, a sample size of 19 schools per group allows detection of a reduction in caries to 25 % incidence in the test groups, with 80 % power, overall *α* = 0.05 (adjusted for multiple comparisons), and ICC = 0.01. For caries incidence in the control group of 20 % (the approximate value observed in the pilot study); the same sample size allows detection of a reduction to 12 % in the test groups. To allow for potential withdrawal of schools, one additional school will be recruited in each group; therefore, 60 primary schools will be randomly allocated to three clusters, taking area into account. If the assumption of 30 pupils per school holds, this will give a total sample size of 1800.

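### The microbiota sub-study fixes AMOVA and LEfSe without tying them to the randomised schools, so its between-arm tests can run above the nominal 5%

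*Protocol article*

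**What the plan says.** Under Methods/Design the trial is described thus: "This is a three-arm, multicentre cluster randomised controlled trial (RCT), with blinded outcome assessment". The Randomisation section fixes the unit: "schools will be randomised to Test group 1 (test books only), Test group 2 (test books and fluoride toothpaste), or Control (control books".

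The main trial handles this consistently. The Sample size section says that "the intra-cluster correlation coefficient (ICC) must be considered when calculating sample size". The Method of analysis section specifies multilevel logistic regression for the primary outcome and multilevel logistic or linear regression for secondary outcomes. It does not mention the sub-study outcomes.

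Those outcomes have a separate heading, Sub-study outcomes, and three analysis statements of their own:

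- Distance matrices: "Analysis of Molecular Variance (AMOVA) will be performed to determine if clustering patterns seen in the PCoA plots are statistically supported".
- Individual OTUs: "Differentially abundant OTUs between patient groups of interest will be identified using the LDA Effect Size (LEfSe) algorithm".
- Proportions of named caries-related taxa: these "will be compared across intervention groups using appropriate statistical tests depending on the data distribution".

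None of the three mentions school. The Research questions section asks about the microbiota in two pairwise comparisons: Control against Test group 1, and Test group 1 against Test group 2.

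On size, the section on the sub-study sample states: "It is expected that the Scottish cohort of the trial will include around 400 children". About half of their parents (n = 200) are expected to consent.

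**The concern.** AMOVA in its usual form permutes samples freely between groups, and LEfSe in its usual form applies rank tests to samples. Both take the child as the independent unit. Here every child in a school has the same allocation, so anything that makes children in a school alike is also shared within an arm.

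The protocol's own procedures make such likeness plausible. A nurse visits each school, collects saliva from small groups of children, and packs and transports the samples together. With only a few schools per arm, differences between schools do not average out and can look like an effect of the books or the toothpaste. What is at stake is the validity of the significance statements for the two microbiota questions.

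**Working it through.** **1. Does the main trial allow for clustering?** This is checked first as a reference. Inputs from Sample size: 35% v 25% (or 20% v 12%), 80% power, 30 pupils per school, ICC 0.01. The form of multiplicity adjustment is not given; I assume two-sided α = 0.05/3.

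- n per arm = [z(1−α/2)·√(2p̄(1−p̄)) + z(0.80)·√(p1(1−p1) + p2(1−p2))]² / (p1−p2)² = 438.3, so 439, for both pairs of rates.
- Design effect = 1 + (30 − 1) × 0.01 = 1.29.
- 439 × 1.29 = 566.3, and 566.3 / 30 = 18.9, so 19 schools per arm, as stated.

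The main trial does build school into its design. The gap is confined to the sub-study.

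**2. How many schools are in the sub-study?** The article does not say. From its own figures of about 400 Tayside children, 30 pupils per school, and 2000–2600 children in 60 schools:

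- 400 / 30 = 13.3 schools
- 400 / (2000/60) = 12 schools
- 400 / (2600/60) = 9.2 schools

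That is about 9–13 schools, or 3 to 5 per arm. With about 200 consenting children, I take 3 schools of 22, 4 of 17 and 5 of 13 per arm (198, 204 and 195 children over three arms).

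**3. Type I error of a test that ignores school, for one outcome.** With m children per school, the design effect is DE = 1 + (m − 1) × ICC. The true rejection rates at nominal 5% are approximately:

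- pairwise: 2 × [1 − Φ(1.96/√DE)]
- three-arm: P(χ² on 2 df > 5.99/DE) = exp(−2.996/DE)

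| Schools per arm × children | ICC | DE | Pairwise | Three-arm |
|---|---|---|---|---|
| 3 × 22 | 0.01 | 1.21 | 7.5% | 8.4% |
| 3 × 22 | 0.05 | 2.05 | 17.1% | 23.2% |
| 3 × 22 | 0.10 | 3.10 | 26.6% | 38.0% |
| 4 × 17 | 0.01 | 1.16 | 6.9% | 7.6% |
| 4 × 17 | 0.05 | 1.80 | 14.4% | 18.9% |
| 4 × 17 | 0.10 | 2.60 | 22.4% | 31.6% |
| 5 × 13 | 0.01 | 1.12 | 6.4% | 6.9% |
| 5 × 13 | 0.05 | 1.60 | 12.1% | 15.4% |
| 5 × 13 | 0.10 | 2.20 | 18.6% | 25.6% |

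At ICC 0, DE = 1 and both rates are 5%. A simulation of 20,000 null trials per cell (normal outcome, school random effect, F test on children) agreed with every cell to within one percentage point. The F test on school means rejected in 4.6–5.2% of trials throughout.

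The value 0.01 is the only ICC in the article. It was set for caries: "a value of 0.01 was used, based on unpublished data collected by the authors". The values 0.05 and 0.10 are my assumptions, to show the range.

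**4. Can whole-school permutation reach significance?** Three v three schools gives C(6,3) = 20 allocations and a smallest two-sided p of 2/20 = 0.10. Four v four gives C(8,4) = 70 and 2/70 = 0.029. Three arms of three give 9!/(3!)³ = 1680 allocations and 6/1680 = 0.004. With 3 schools per arm, only the three-arm permutation test can fall below 0.05.

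**The case against.** The article promises a detailed statistical analysis plan, and a protocol article may leave detail to it. That answers silence, but not the naming of two procedures which, in standard form, do not match the design. The multilevel commitment covers secondary outcomes, and the article lists those separately from the sub-study outcomes.

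Four stronger readings are tempting, and the document does not support them.

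- *All three sub-study analyses ignore school.* No test of taxon proportions is named. Choice by data distribution neither requires nor excludes a mixed model or a comparison of school means.
- *The article says outright that AMOVA and LEfSe compare arms.* It does not. The AMOVA sentence refers to patterns in the ordination plots, and the LEfSe sentence to groups of interest. That they test arms is an inference from the research questions. It is a sound one, but still an inference.
- *The baseline saliva sample is discarded.* The article collects saliva at baseline and at two years and does not say which time points enter which comparison. That is an unstated detail, not a stated choice.
- *The AMOVA p-values are certainly invalid.* A simulated AMOVA-type test with free permutation (13 schools of 15 children) rejected a true null in 16% of runs at ICC 0.01 and 79% at 0.05. It assumed 20 independent dimensions that all share one ICC, and nothing in the article supports that structure. It shows that a multivariate test may fare worse than a single outcome, but it does not give the size.

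It also stands that the inflation depends on a correlation the article does not report, and that it is small for one taxon at ICC 0.01.

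**Conclusion.** The point holds in a conditional form. The article fixes AMOVA and LEfSe for a comparison of randomised schools and makes no allowance for school, although it does so for the primary and secondary outcomes.

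For one outcome, with 3 to 5 schools per arm and about 200 children, a nominal 5% pairwise test that ignores school would run at about 6–8% (ICC 0.01), 12–17% (0.05) or 19–27% (0.10). A three-arm test would run at about 7–8%, 15–23% or 26–38%. The pairwise figures are the relevant ones, because both microbiota questions are pairwise. All of them rest on assumed school numbers and ICCs, equal cluster sizes and one normally distributed outcome.

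Severity is moderate. The primary and secondary conclusions of the trial are untouched.

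**What to change.** State under Sub-study outcomes that every between-arm microbiota comparison respects school randomisation, and report the number of Tayside schools per arm.

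1. Run AMOVA with arm labels permuted over whole schools. Where only 3 schools per arm remain, use the three-arm test, because 3 v 3 cannot reach p < 0.05. Pairwise differences on the distance scale are then descriptive.
2. Compare taxon proportions with a mixed model that has a school random effect and a small-sample degrees-of-freedom correction, or compare school means.
3. Keep LEfSe as description, without between-arm significance claims.

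The cost is wording and modest analysis work; data collection does not change. The downside is wider intervals and fewer nominally significant taxa, which reflects how little information 3 to 5 schools per arm carry.
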